## SEARCH-AF Protocol Summary of Changes (Document date: June 30 2020)

Amendment 3: Version 3.0 (01-Oct-2018) vs. Version 4.0 (30-Jun-2020)

| Protocol Section |                           | Description of Changes                                                                                                                                                                                                                                                                                                                                                                              | Reason / Rationale                                                                                                                                                                                                                                                                                                                                                                                                                                                  |
|------------------|---------------------------|-----------------------------------------------------------------------------------------------------------------------------------------------------------------------------------------------------------------------------------------------------------------------------------------------------------------------------------------------------------------------------------------------------|---------------------------------------------------------------------------------------------------------------------------------------------------------------------------------------------------------------------------------------------------------------------------------------------------------------------------------------------------------------------------------------------------------------------------------------------------------------------|
| Page 15          | Secondary Objectives (#3) | 
Previous wording: "To assess subjects' adherence and incidence of adverse events from use of the Medtronic SEEQ™ system."
 
Revised wording: "To assess subjects' adherence and incidence of adverse events from use of the Medtronic SEEQ™ system or the CardioStat® cardiac rhythm monitoring device."
                                                                                | Use of the CardioSTAT® cardiac rhythm monitoring device in this trial was implemented on October 1 2018 as the Medtronic SEEQ™ device was phased out by the company. Wording pertaining to CardioSTAT® was included in protocol version 3.0 (dated 01-Oct-2018). Due to oversight, inclusion of this wording was not done for this specific secondary objective. Accordingly, this has been included in protocol version 4.0.                                       |
| Page 28          | Secondary Outcomes (#1)   | 
Previous wording: "AF/AFL lasting for <math>\geq 24</math> hours during 30 days after randomization and at <math>6\pm 1</math> months after surgery."
 
Revised wording: "AF/AFL lasting for <math>\geq 24</math> hours during 30 days after randomization and between day 31 and the last follow-up date."
                                                                             | Due to the COVID-19 pandemic, study visits could not be conducted at the specified time windows for some of the study participants. Therefore, wording has been revised to account for the fact that study visits and collection of outcomes during follow-up visits could have been conducted outside the pre-specified time windows for some participants.                                                                                                        |
| Page 28          | Secondary Outcomes (#2)   | 
Previous wording: "Cumulative AF/AFL burden during the 14-day monitoring period (recorded by the wearable adhesive cardiac monitoring device) at <math>6\pm 1</math> months after surgery."
 
Revised wording: "Cumulative AF/AFL burden during the 14-day monitoring period (recorded by the wearable adhesive cardiac monitoring device) between day 31 and the last follow-up date."
 | Due to the COVID-19 pandemic, study visit #2 (originally planned at $6\pm 1$ months after surgery) could not be conducted at the specified time window for some of the study participants. As a result, some subjects did not undergo cardiac rhythm monitoring at $6\pm 1$ months after surgery. Therefore, wording has been revised to account for the fact that cardiac rhythm monitoring was conducted outside the $6\pm 1$ month window for some participants. |
| Page 28          | Secondary Outcomes (#3)   | 
Previous wording: "Proportion of subjects who are prescribed with oral anticoagulation at the following timepoints: (i) 45 days after discharge from cardiac surgery; (ii) <math>6\pm 1</math> months after discharge from cardiac surgery; (iii) <math>9\pm 1</math> months after discharge from cardiac surgery. "
                                                                         | Due to the COVID-19 pandemic, study visits could not be conducted at the specified time windows for some of the study participants. Therefore, wording has been revised to account for the fact that study visits and collection of outcomes during follow-up visits could have been conducted outside the pre-specified time                                                                                                                                       |

## SEARCH-AF Protocol Summary of Changes (Document date: June 30 2020)

### Amendment 3: Version 3.0 (01-Oct-2018) vs. Version 4.0 (30-Jun-2020)

| Protocol Section |                         | Description of Changes                                                                                                                                                                                                                                           | Reason / Rationale                                      |
|------------------|-------------------------|------------------------------------------------------------------------------------------------------------------------------------------------------------------------------------------------------------------------------------------------------------------|---------------------------------------------------------|
|                  |                         | Revised wording: "Proportion of subjects who are prescribed with oral anticoagulation at the following timepoints: (i) 45 days after discharge from cardiac surgery; (ii) between day 46 and the last follow-up date."                                           | windows for some participants.                          |
| Page 28          | Secondary Outcomes (#4) | 
Previous wording: "Number of days during which the wearable adhesive cardiac rhythm monitor sensor was worn by subjects."
 
Revised wording: "Number of days during which the wearable adhesive cardiac rhythm monitor sensor was worn by subjects."
 | There was a typo ("wearable") which has been corrected. |

**Date**

## **1. INTRODUCTION**

This statistical analysis plan (SAP) outlines the planned statistical methods for the summary and analysis of data collected within the scope of the Post-Surgical Enhanced Monitoring for Cardiac Arrhythmias and Atrial Fibrillation (SEARCH-AF) trial protocol version 4.0 dated June 30 2020.

The SAP should be read in conjunction with the study protocol and the electronic Case Report Forms (eCRFs). This version of the SAP has been developed using the final version of the protocol mentioned above and eCRFs version 8.5.11 dated September 5, 2019.

All statistical analyses will be performed using R version 3.6.2, or higher.

## **2. STUDY OBJECTIVES**

### **2.1 Primary Objective**

To test whether enhanced cardiac rhythm monitoring with an adhesive, continuous monitoring device results in higher rates of atrial fibrillation/atrial flutter (AF/AFL) detection during the subacute, post-discharge period of cardiac surgical subjects who are at risk of developing post-operative atrial arrhythmias, when compared to usual care.

#### **Primary Outcome and Endpoint**

The primary outcome of this trial is the difference in proportions of participants with a cumulative atrial fibrillation/flutter (AF/AFL) duration of  $\geq 6$  minutes or documentation of AF/AFL by a 12-lead electrocardiogram (ECG) between groups. The primary endpoint of this trial is documentation of sustained AF/AFL, defined as a cumulative AF/AFL duration of  $\geq 6$  minutes or documentation of AF/AFL by a 12-lead ECG within 30 days after randomization. Clinical endpoints will be adjudicated by an independent clinical events committee.

### **2.2 Secondary Objectives**

To compare the following secondary outcomes between the enhanced cardiac rhythm monitoring group and the usual care group:

#### **2.2.1 Secondary Outcomes**

- 1) Proportion of subjects with detection of cumulative AF/AFL lasting for  $\geq 24$  hours at the following time points:
  - i. within the first 30 days after randomization
  - ii. between day 31 and the last follow-up date
- 2) Duration of cumulative AF/AFL burden detected during the 14-day monitoring period (recorded by the wearable adhesive cardiac monitoring device) among subjects:

- i. between day 31 and the last follow-up date
- 3) Proportion of subjects who are prescribed oral anticoagulation at the following time points:
  - i. within the first 45 days after discharge from surgery
  - ii. between day 46 and the last follow-up date
- 4) Number of days during which the protocol-mandated wearable cardiac rhythm monitor sensor was worn by subjects.
  - i. within the first 30 days after randomization (note: applicable for enhanced cardiac monitoring group only)
  - ii. between day 31 and the last follow-up date
- 5) Reasons for premature removal of protocol-mandated wearable adhesive cardiac rhythm monitors by subjects.
- 6) Proportion of subjects who experienced adverse events related to the use of protocol-mandated wearable adhesive cardiac rhythm monitors at the following time points:
  - i. within the first 30 days after randomization
  - ii. between day 31 and the last follow-up date
- 7) Performance of non-protocol mandated Holter monitoring and/or event recorders during the 30-day period after randomization.
  - i. within the first 30 days after randomization
- 8) Proportion of subjects who experienced major adverse cardiac event (MACE) outcomes (ALL-cause death, myocardial infarction, ischemic stroke, non-CNS system embolism) at the following time points:
  - i. within the first 45 days after discharge from surgery
  - ii. between day 46 and the last follow-up date
- 9) Proportion of subjects with major bleeding events at the following time points:
  - i. within the first 45 days after discharge from surgery
  - ii. between day 46 and the last follow-up date
- 10) Hospitalization or emergency room visits.
  - i. within the first 45 days after hospital discharge from index cardiac surgery
  - ii. between day 46 and the last follow-up date

*(note: This secondary outcome was listed in the original clinicaltrials.gov submission dated on June 2 2016 but was not explicitly listed in the protocol).*

- 11) Proportion of subjects with cumulative AF/AFL lasting for  $\geq 6$  hours at the following time points:
  - i. within the first 30 days after randomization
  - ii. between day 31 and the last follow-up date

*(note: this secondary outcome was pre-specified before data lock and data analysis but was not explicitly listed in the protocol).*

To describe the following outcomes in the enhanced cardiac rhythm monitoring group and/or the usual care group:

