### **2.2 Secondary Objectives:**

- 1) To assess the incidence of AF/AFL of cardiac surgical subjects during: (i) the subacute, post-discharge period and (ii) late period (6±1 months after surgery).
- 2) To assess the proportion of subjects with continuous AF and/or AFL lasting ≥ 24 hours during the subacute, post-discharge period of subjects after cardiac surgery.
- 3) To assess subjects' adherence and incidence of adverse events from use of the Medtronic SEEQ™ system or the CardioStat® cardiac rhythm monitoring device.
- 4) To assess the proportion of subjects who are prescribed with oral anticoagulation at 45 days after discharge, at 6±1 months, and at 9±1 months from cardiac surgery.
- 5) To assess the proportion of subjects who experienced major bleeding events during the 45 day-period after discharge from cardiac surgery.

- 6) To evaluate factors associated with development of POAF/AFL during the subacute, post-discharge period of subjects after cardiac surgery.

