## 5.12 Secondary Outcomes

- 1) AF/AFL lasting for  $\geq 24$  hours during 30 days after randomization and between day 31 and the last follow-up date.
- 2) Cumulative AF/AFL burden during the 14-day monitoring period (recorded by the wearable adhesive cardiac monitoring device) between day 31 and the last follow-up date.
- 3) Proportion of subjects who are prescribed with oral anticoagulation at the following timepoints: (i) 45 days after discharge from cardiac surgery; (ii) between day 46 and the last follow-up date.
- 4) Number of days during which the wearable adhesive cardiac rhythm monitor sensor was worn by subjects.
- 5) Reasons for premature removal of the wearable adhesive cardiac rhythm monitor by subjects.
- 6) Incidence of adverse events related to use of the wearable adhesive cardiac rhythm monitor.
- 7) Performance of non-protocol mandated Holter monitoring and/or event recorders during the 30-day period after randomization (for subjects in both groups).
- 8) Major adverse cardiac outcomes occurring within 45 days after hospital discharge, including the following: all-cause death, myocardial infarction, ischemic stroke, non-CNS systemic embolism (please refer to appendix H for endpoint definitions).
- 9) Proportion of subjects who experienced major bleeding events (please refer to appendix I for definitions of bleeding outcomes) within 45 days after discharge from cardiac surgery.

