## 12.2 Details of Statistical Analysis

Descriptive statistics will be computed. For continuous variables, mean  $\pm$  standard deviation will be reported or median and interquartile range as appropriate. For categorical variables, counts  $\pm$  percentages will be reported.

The primary analysis will be conducted with the intent-to-treat principle. The primary outcome will be displayed in a 2 x 2 contingency table, sorted according to randomization status (intervention/control group) and the presence/absence of the primary endpoint. A contingency table stratified by the surgery type stratification factor will also be examined for homogeneity of treatment effect. The number of AF/AFL episodes will be compared by means of a Poisson regression model (or possibly zero-inflated Poisson if indicated) and the treatment effect expressed as a rate ratio with 95% CI. The proportion of patients experiencing AF/AFL lasting for 24 hours or more will be compared with a Fisher's Exact test (because numbers of events and therefore expected cell counts are expected to be low). The treatment effect will be expressed as a difference in proportions with 95% CI. The proportions of patients prescribed with oral anticoagulants will be analyzed similarly.

Since outcomes related to the device itself do not have a comparison group, they will be analyzed using only descriptive statistics (means, proportions, etc.). All remaining secondary outcomes are binary and will be compared with a Fisher's Exact test (assuming the assumptions for the chi-square test are not met) and the treatment effects will be expressed as risk differences with 95% CIs. Given the expected very low attrition rate of 2%, any missing data resulting from attrition at that rate will be insufficient to substantially alter conclusions. Nevertheless some sensitivity analyses will be considered, especially given anticipated low event rates.

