## MEMO

**To:** All site investigators and coordinators of the SEARCH-AF study

**Subject:** PROTOCOL CLARIFICATION

**Date:** Monday February 6, 2017

---

The purpose of this memorandum is to clarify the following in the SEARCH-AF study protocol (Version Number: 1.0, Version Date: 18 December, 2015):

The primary and secondary study '*objectives*' are listed in two areas of the protocol:

- Page 7
- Page 15

The primary and secondary study '*outcomes*' are listed on:

- Page 27

Please note that there are slight wording differences between the listed '*objectives*' and '*outcomes*', and that all study endpoints will be measured in accordance to the definitions on page 27.

Please file this memo with your SEARCH-AF regulatory files.

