### **2.2.2 Descriptive Outcomes**

- 1) Proportion of subjects who are prescribed oral anticoagulation at the following time points:
  - i. within the first 30 days after randomization
- 2) Proportion of subjects with cumulative AF/AFL lasting for  $\geq 6$  minutes at the following time points:
  - i. within the first 30 days after randomization
  - ii. between 31 days and the last follow-up date
- 3) Proportion of subjects with detection of at least 1 episode of AF/AFL lasting for  $\geq 30$  seconds:
  - i. within the first 30 days after randomization
- 4) Proportion of subjects with detection of at least 1 episode of AF/AFL lasting for  $\geq 6$  minutes on a continuous basis at the following time points:
  - i. within the first 30 days after randomization
  - ii. between 31 days and the last follow-up date
- 5) Proportion of subjects with detection of at least 1 episode of AF/AFL lasting for  $\geq 6$  hours on a continuous basis at the following time points:
  - i. within the first 30 days after randomization
  - ii. between 31 days and the last follow-up date
- 6) Proportion of subjects with detection of at least 1 episode of AF/AFL lasting for  $\geq 24$  hours on a continuous basis at the following time points:
  - i. within the first 30 days after randomization
  - ii. between 31 days and the last follow-up date
- 7) For each subject, the total number of AF/AFL episodes lasting for  $\geq 6$  minutes on a continuous basis at the following time points:
  - i. within the first 30 days after randomization
  - ii. between 31 days and the last follow-up date

- 8) For each subject, the total number of AF/AFL episodes lasting for  $\geq 6$  hours on a continuous basis at the following time points:
  - i. within the first 30 days after randomization
  - ii. between 31 days and the last follow-up date
- 9) For each subject, the total number of AF/AFL episodes lasting for  $\geq 24$  hours on a continuous basis at the following time points:
  - i. within the first 30 days after randomization
  - ii. between 31 days and the last follow-up date
- 10) Proportion of subjects with at least one 12-lead ECG demonstrating AF/AFL at the following time points:
  - i. within the first 30 days after randomization
  - ii. between 31 days and the last follow-up date
- 11) Proportion of subjects who underwent non-protocol mandated continuous cardiac rhythm Holter monitoring and/or event recorders at the following time points:

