### **4.2 Secondary Analysis**

For the secondary outcomes outlined in section 2.2.1, a chi-squared test of independence will be used to compare the proportions between groups where appropriate. Difference in proportions, the 95% confidence intervals, and p values will be reported.

For the descriptive outcomes outlined in section 2.2.2, only descriptive summaries will be presented. Mean and standard deviations or median with interquartile range (where appropriate) will be reported for continuous outcomes. Counts and percentages will be reported for categorical outcomes. No inferential analyses of these outcomes are planned unless they are specifically requested during the peer-review process and deemed appropriate by the statistical team.

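### The SAP compares arms on cumulative AF/AFL of 24 hours or more and leaves the protocol's continuous 24-hour objective with no planned comparison

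*Supplement*

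**What the plan says.** Protocol v4.0 gives secondary objective 2 in the synopsis and again in section 2.2: "To assess the proportion of subjects with continuous AF and/or AFL lasting" 24 hours or more. Its outcomes list (5.12, item 1) uses neither *continuous* nor *cumulative*. It refers to AF/AFL lasting 24 or more "hours during 30 days after randomization and between day 31 and the last follow-up date". The next item in that list does name a sum: "Cumulative AF/AFL burden during the 14-day monitoring period". Section 12.2 commits to a test: "The proportion of patients experiencing AF/AFL lasting for 24 hours or more will be compared with a" Fisher's exact test, chosen because few events are expected, with a difference in proportions and 95% CI.

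A memo of 6 February 2017, written for protocol v1.0, notes small wording differences between objectives and outcomes and says that "all study endpoints will be measured in accordance to the definitions on page 27", meaning the outcomes list.

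The SAP, written for v4.0, defines secondary outcome 1 (2.2.1) as the "Proportion of subjects with detection of cumulative AF/AFL lasting for" 24 hours or more, in two windows: the first 30 days after randomization, and day 31 to last follow-up. The unbroken version is descriptive outcome 6 (2.2.2): "Proportion of subjects with detection of at least 1 episode of AF/AFL lasting for" 24 hours or more on a continuous basis, in the same windows. SAP 4.2 then states: "For the descriptive outcomes outlined in section 2.2.2, only descriptive summaries will be presented".

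**The concern.** Followed as written, the SAP never compares the arms on the 24-hour objective that the protocol states. The tested quantity is total time in AF/AFL, which many short episodes can reach. The stated objective concerns a single long episode.

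The SAP notes that outcomes 10 and 11 were not explicitly listed in the protocol, and outcome 11 (cumulative 6 hours or more) is the same kind of measure. Outcome 1 carries no such note, so a reader of the results would take the cumulative figure for the protocol's own outcome. Because few events are expected, reclassifying a handful of subjects could change what is reported.

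**Working it through.** **1. Is the continuous reading the more natural one?** The protocol text, side by side:

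- Objective 2 (synopsis and 2.2): continuous, 24 hours or more.
- Outcome 1 (5.12) and section 12.2: lasting 24 hours or more, with no qualifier.
- Primary endpoint (5.11) and outcome 2 (5.12): the word *cumulative* is written out.
- Exclusion criterion 3: continuous AF/AFL of 24 hours or more.
- Amendment 3 (June 2020): reworded outcome 1, changing only the time window.

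The protocol writes *cumulative* where it means a sum, and did not add it to outcome 1 when that outcome was last edited. Beside a continuous objective, the unqualified wording reads most naturally as one unbroken episode, but the list does not say so. The SAP carries both versions separately, so it treats them as different quantities.

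**2. Direction of the change.** Any subject with one unbroken episode of 24 hours or more also has at least 24 hours in total. So, in each arm and each window, cumulative count ≥ continuous count. How far the threshold can be spread:

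- 30-day recording: 24 × 60 / 30 = 48 minutes a day on average.
- 28-day recording (two CardioStat devices): 24 × 60 / 28 = 51 minutes a day.
- 14-day late recording: 24 × 60 / 14 = 103 minutes a day.

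These figures describe the threshold. They do not measure how many subjects would be reclassified.

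**3. Who can accrue the event.**

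- Days 0–30: the intervention arm is recorded for 28 to 30 days; controls have no mandated continuous monitoring. Adding up separate episodes needs long recording, so the cumulative definition may add to the difference in detection.
- From day 31: both arms have the same planned 14 days of monitoring. Neither is favoured by design.

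**4. Sensitivity to a few events.** The plan's only powered figure is for the primary endpoint, and it reproduces. With rates of 3% and 10%, two-sided alpha 0.05, 80% power and pooled proportion 0.065:

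n = [1.960·√(2 × 0.065 × 0.935) + 0.842·√(0.03 × 0.97 + 0.10 × 0.90)]² / 0.07² = 193.5, so 194 per arm; 194 / 0.98 = 198 per arm, 396 in total.

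The documents give no rate for 24-hour AF/AFL under either definition. As an illustration, assume 198 per arm and no control events. With k intervention events, two-sided Fisher p = 2·C(198,k)/C(396,k):

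| Intervention events | Fisher | Chi-squared, uncorrected | Chi-squared, corrected |
|---|---|---|---|
| 4 | 0.123 | 0.044 | 0.132 |
| 5 | 0.061 | 0.024 | 0.072 |
| 6 | 0.030 | 0.014 | 0.040 |

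One or two reclassified subjects can move the result across 0.05. So can the test: protocol 12.2 names Fisher's exact test for this outcome, while SAP 4.2 names a chi-squared test where appropriate and does not mention a continuity correction.

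**The case against.** The strongest reply is that the SAP overwrote nothing. By the 2017 memo the outcomes list governs, and that list says neither *continuous* nor *cumulative*. The SAP had to settle an open wording and chose the form that matches the primary endpoint, itself cumulative. The continuous measure is still reported: descriptive outcome 6 gives the proportion in both windows, and descriptive outcome 9 counts such episodes. Much of this stands. The memo addresses v1.0, however, and v4.0 still carries both wordings. Even under the memo, the SAP resolved the wording against the stated objective without saying so, and the continuous version lost its planned test and interval.

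A reader might also infer that the cumulative definition was a swap that favours the monitored arm. The documents do not support that. From day 31 the planned monitoring is equal. In the first 30 days, documenting an unbroken 24-hour episode also needs at least 24 hours of recording, so the continuous version suffers unequal detection too. A 24-hour Holter meets either definition only if AF/AFL is present throughout; a 48-hour Holter meets the cumulative one with AF/AFL for 24 / 48 = 50% of the recording. Unequal detection is the trial's acknowledged question (protocol 5.7), not something this choice introduces.

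Nor do the guidelines cited in protocol 5.13 settle the matter. One refers to continuous AF beyond 72 hours, one to AF duration beyond 48 hours, and one gives no duration threshold.

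**Conclusion.** The concern holds as an unmarked mismatch of definition. The objective is continuous, the governing outcomes list is silent, the SAP's tested outcome is cumulative, and the continuous version has no planned comparison. It affects one unpowered secondary outcome in two windows and leaves the primary analysis untouched.

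That the cumulative count is equal or larger is true by definition. Any extra advantage to the monitored arm is a possibility confined to the first 30 days, and its size cannot be calculated from the documents. The p-values above rest on an assumed zero control events and show only that small shifts could matter. The conclusion also rests on reading the unqualified wording in 5.12 in the light of the continuous objective, which is the more natural reading but not the only one.

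**What to change.** In SAP 2.2.1(1), make the proportion of subjects with one or more unbroken AF/AFL episodes of 24 hours or longer a between-arm comparison in both windows. Report the difference in proportions, its 95% CI and the Fisher's exact test that protocol 12.2 names for this outcome. Keep cumulative 24 hours beside it, with a note like those on outcomes 10 and 11: that the definition was added in the SAP, why, and when relative to data lock. The cumulative measure need not be demoted.

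The cost is a few lines in the SAP and one further comparison per window. Both measures are already planned, so no new data are needed.
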